### Data management

Research data will be entered and managed using REDCap (Research Electronic Data Capture) hosted by Fujita Health University. Identifiable personal information will be deleted, and only coded and anonymized data will be used. Data will be password-protected, and access will be restricted to authorized research personnel. Data quality will be improved through predefined range checks and routine monitoring by the research team.

### Sample size

This is a pilot study; therefore, the sample size was not calculated based on statistical testing power [16]. We aim to enroll 32 participants, as this is presumed to be an adequate sample size for gathering insights on recruitment, enrollment, adherence, and retention rates. With 32 participants recruited, a retention of 90% can be estimated to within a 95% confidence interval (CI) ranging from 75–96%. This sample size should also suffice to accurately assess means and variances [42] and to provide data regarding clinical outcomes.

### Blinding

Due to the differing treatment programs between the RAGT and CGT groups, it will be challenging to blind participants and therapists with respect to group assignment. Therefore, only the assessors will remain blinded. To quantify the effectiveness of blinding, we will ask the blinded assessors to identify each participant’s group assignment at the conclusion of all assessments.

### Analytical methods

Feasibility results will be reported using descriptive statistics. Recruitment, enrollment, adherence, and retention rates will be computed with 95% confidence intervals. The adverse events and their frequencies will be recorded. Any exclusions or dropouts, along with their reasons and stages of occurrence, will also be recorded. The success of blinding will be detailed as a percentage of correct guesses.

The primary outcome measure will be the incidence of gait independence during the intervention period. The cumulative incidence of gait independence will be analyzed using the Kaplan–Meier method, and the log-rank test will evaluate the significance of differences in the Kaplan–Meier curves between groups. Cumulative incidence of gait independence events at the end of the intervention, along with the median duration from baseline to gait independence attainment, and the restricted mean survival time until the end of the intervention will be calculated. Additionally, to supplement the initial treatment effect analysis, differences will be evaluated using the generalized Wilcoxon test. Individuals who do not achieve gait independence during the intervention period will be censored. Secondary clinical outcomes will encompass gait performance measures, physical function, and activity outcomes at baseline, 4 weeks, 8 weeks, and discharge, alongside the intervention dose. Comparisons between the two groups will utilize the chi-square test for categorical variables and either Student’s *t-*test or Mann–Whitney *U* tests for continuous variables. To evaluate the potential effectiveness of the intervention and gather data useful for future trial design, we will estimate the effect size for the time elapsed from baseline to achieving gait independence, specifically estimating the hazard ratio as a relative measure of the likelihood of achieving gait independence over time.

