We defined the “acute” phase as the period occurring within 7 days of stroke onset [14] and have planned a study to clarify the efficacy of RAGT initiated during this timeframe. We hypothesize that the initiation of RAGT in the acute phase would enable individuals to achieve gait independence more rapidly than with CGT. Early RAGT promotes motor learning and mitigates disuse by delivering high-intensity, task-oriented gait training from an early stage [9, 15]. To test this hypothesis, we aim to examine the following: (i) the feasibility of conducting a randomized controlled trial on RAGT for improving gait after acute stroke and (ii) obtaining preliminary estimates of the potential efficacy of RAGT for achieving gait independence during the acute phase.

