#### Clinical outcomes

The Standard Protocol Items: Recommendations for Interventional Trials (SPIRIT) diagram presented in Fig. 4 summarizes the data collection schedule. Furthermore, we have included the SPIRIT 2013 checklist as an additional file, comprising recommended items to address in a clinical trial protocol. Blinded assessors will perform assessments weekly after the baseline assessment until participants achieve an FAC score of ≥ 3. Continuous weekly assessments will be terminated once the participants achieve an FAC score of ≥ 3 or when they undergo the intervention for 8 weeks. However, assessments at 4 and 8 weeks and discharge will always be performed, regardless of whether an FAC score of ≥ 3 is achieved. The blinded assessments will be conducted by three physical therapists with > 10 years of experience. The assessors will confirm the assessment methods sufficiently prior to the commencement of the study.

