**Fig. 4 Fig4:**
[figure not shown]
SPIRIT figure Note: * Items to be assessed if the Functional Ambulation Category score is ≥3. SIAS, Stroke impairment assessment set

The primary clinical outcome measures will include the number of days from the baseline assessment to the achievement of gait independence and the percentage of individuals achieving gait independence—operationally defined as an FAC score ≥ 3. In particular, this primary clinical outcome represents the most promising candidate for future clinical trial endpoints. Secondary clinical outcomes encompass gait parameters as assessed by velocity, stride length, and cadence in the 10-m walk test; 6-min walk distance; SIAS scores for lower limb motor and trunk function; total score on the Functional Independence Measure (FIM); and the number of steps taken during gait training during the intervention period. The FAC is a reliable and validated clinical measure of gait ability based on the amount of assistance needed [20, 21]. The 10-m walk test is a reliable and validated clinical measure of walking ability [33, 34], whereas the 6-min walk test is a reliable and validated clinical measure of motor endurance [35, 36]. The number of steps taken during gait training will be recorded manually by a therapist using a counting device. The SIAS serves as a reliable and validated index for assessing functional impairment in patients with stroke [17–19]. It accounts for motor function, tension, sensory function, range of motion, pain, trunk function, higher brain function, and muscle strength on the non-paralyzed side, with total scores ranging 0–72. The total score for SIAS motor items is calculated as the sum of the hip flexion, knee extension, and foot pat tests, with scores ranging 0–15 points. The FIM, which comprises 13 motor items and 5 cognitive items, is a proven reliable index for assessing independence in activities of daily living [37, 38]. Each item is rated on a scale of 1–7, with scores of 1–4 indicating the need for varying levels of physical assistance, a score of 5 indicating the need for supervision, a score of 6 indicating modified independence, and a score of 7 indicating complete independence. The FIM cognitive total is the sum of scores of the five cognitive items, ranging 5–35 points.

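### A single percentage of correct guesses, taken once recovery is known, cannot separate real unblinding of assessors from guessing by recovery or from one-sided guessing

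*Protocol article*

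**What the plan says.** Assessors are the only masked role. The Blinding section explains that participants and therapists cannot readily be masked and concludes: "Therefore, only the assessors will remain blinded". To measure how well this worked, assessors are asked to name each participant's "group assignment at the conclusion of all assessments". Analytical methods then fixes the summary: "The success of blinding will be detailed as a percentage of correct guesses".

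The people who guess also rate the outcome. Under Clinical outcomes: "Blinded assessors will perform assessments weekly after the baseline assessment until participants achieve an FAC score of ≥ 3". Further assessments follow at 4 weeks, 8 weeks and discharge in every case. The same section states: "The blinded assessments will be conducted by three physical therapists with > 10 years of experience". The primary clinical outcome is gait independence, "operationally defined as an FAC score ≥ 3". The Background gives the trial's hypothesis, that early RAGT "would enable individuals to achieve gait independence more rapidly than with CGT".

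**The concern.** The stated purpose of the guess is to quantify how effective the blinding was. The stated measure, at the stated time, does not do that cleanly, for two reasons.

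- **One-sided guessing is hidden.** Guessing the same arm for everyone is right in one arm and wrong in the other. In an overall percentage the two cancel.
- **Recovery is itself a clue.** By the time of the guess the assessors have scored FAC. Weekly visits also stop once FAC 3 is reached, so the visit schedule shows who recovered early. The trial's hypothesis links faster recovery to RAGT, so guessing RAGT for those who recovered is a foreseeable strategy. If RAGT works, that strategy beats 50% although nobody has learned the allocation.

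FAC is rated by these assessors and the pilot is meant to inform a larger trial. A misreading in either direction could therefore colour later views on how the outcome should be assessed.

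**Working it through.** **Inputs.** From the document: 32 participants (Sample size), two arms, guesses collected per participant, three assessors. Assumed, because not stated: 16 per arm, one guess per participant, and all recovery and leakage rates below.

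**The plan's own figure.** No figure is given for blinding. The only interval in the article is 75–96% for 90% retention with 32 participants. The Wilson formula reproduces it:

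[p + z²/(2n) ± z√(p(1−p)/n + z²/(4n²))] / (1 + z²/n), with p = 0.90, n = 32, z = 1.96, gives 75.0% to 96.4%.

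The same formula is used for percentages below.

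**Step 1: one-sided guessing.** Overall percentage = (correct in RAGT + correct in CGT)/32. Bang index per arm = (correct − wrong)/guesses in that arm, so 0 is chance, +1 is all correct and −1 is all wrong.

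| Pattern | RAGT correct | CGT correct | Overall | Index RAGT | Index CGT |
|---|---|---|---|---|---|
| Coin-flip | 8/16 | 8/16 | 50% | 0 | 0 |
| Tilt towards RAGT | 12/16 | 4/16 | 50% | +0.5 | −0.5 |
| RAGT for everyone | 16/16 | 0/16 | 50% | +1 | −1 |

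All three have the same overall figure and the same 95% CI (34–66%). Only the split by arm tells them apart.

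**Step 2: guessing by recovery, blinding intact.** If assessors guess RAGT for everyone who reached FAC 3 or more and CGT for the rest:

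- overall correct = 0.5·p_RAGT + 0.5·(1 − p_CGT)
- index in RAGT = 2·p_RAGT − 1; index in CGT = 1 − 2·p_CGT

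If instead a fraction q of allocations is truly known and the rest are coin-flips:

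- overall correct = q + (1 − q)/2 = 0.5 + q/2, and the index is q in both arms.

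| Assumed recovery, RAGT v CGT | Overall correct | Index RAGT | Index CGT | True leakage q with the same overall figure |
|---|---|---|---|---|
| 50% v 50% | 50% | 0 | 0 | 0% |
| 60% v 40% | 60% | +0.2 | +0.2 | 20% |
| 70% v 50% | 60% | +0.4 | 0 | 20% |
| 80% v 40% | 70% | +0.6 | +0.2 | 40% |

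For 70% v 50%: 0.5 × 0.70 + 0.5 × 0.50 = 0.60. For q = 0.20: 0.5 + 0.10 = 0.60.

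The 60% v 40% row shows that a split by arm alone is not enough. Its indices, +0.2 and +0.2, equal those of 20% true leakage.

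**Step 3: split by FAC status as well.** Among those who reached FAC 3 or more, a pure recovery-guesser says RAGT for all. The index is +1 in RAGT and −1 in CGT, which sum to 0. Among those who did not, it is −1 and +1, again summing to 0. Leakage of 20% unrelated to recovery gives +0.2 in every cell, so the two arms sum to +0.4. The expected patterns now differ.

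**Step 4: precision.** With 32 independent guesses, 22 correct gives an exact two-sided p of 0.0501 and 23 correct (72%) gives 0.020. An overall 60% has a Wilson CI of 43–75%. For an index near 0 with 16 per arm, SE = 1/√16 = 0.25 and the 95% half-width is 1.96 × 0.25 = 0.49. Split by FAC status, cells average 32/4 = 8 guesses and the half-width is 1.96/√8 = 0.69. Clustering of guesses within three assessors may widen these further.

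**The case against.** The best case against the point has four parts.

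- **The article does not say that the arms are pooled.** That is inferred from the wording, which describes one percentage. Guesses are collected per participant, and arm and FAC are recorded anyway, so a table by arm and by FAC status could be made from data already planned. This stands, and it is why the point is worded for the single-percentage reading. It does not remove the point, because the article names a measure and a time, and that pairing does not serve the purpose it states. The reason for a guess and a 'do not know' answer have to be collected when the guess is made.
- **Nothing hangs on the result.** A reader might infer that this check decides whether the primary outcome can be trusted, or that the pilot will declare blinding failed or upheld. The document supports neither. It sets no threshold or test for blinding, which is not one of the four progression criteria and is not among the quantities the Discussion names for designing the next trial. Clinical findings are already called exploratory.
- **Asking at the end is defensible.** An earlier question might prompt assessors to think about allocation while still scoring FAC. The article does not give this reason, but the timing is a trade-off and should not be called an error.
- **The scenarios are extreme and the sample is small.** Step 2 assumes that every assessor follows the recovery rule for every participant, which is the most this mechanism can produce. The 41–85% in the Background is a general range of gait recovery after stroke and gives no contrast between arms. The proposed table is also imprecise. All of this stands.

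**Conclusion.** The point holds as a minor one. A single overall percentage of correct guesses, collected after the outcome is known, cannot tell random from one-sided guessing (both can give 50%). Nor can it tell real unblinding from guessing by recovery (60% under either assumed scenario). That follows from the arithmetic. How large the distortion would be in this trial depends on the assumed 16:16 split, the assumed recovery rates and how consistently assessors guess from recovery, none of which the document gives.

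The sample size, the primary analysis and the progression criteria are untouched. What is at stake is a misread blinding result in a pilot whose purpose is to inform a later trial. It would go too far to conclude that blinding is likely to fail, or that the FAC ratings are unreliable; nothing in the document shows either.

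**What to change.** Keep the guess at the end of all assessments. Add two response items: a 'do not know' option, and the reason for the guess (for example seen or told, or inferred from recovery). In Analytical methods, replace the single percentage with:

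- guesses tabulated by arm, with the Bang index and its 95% CI for each arm ('do not know' counted in the denominator as neither right nor wrong);
- the same table split by whether FAC 3 or more was reached;
- the stated reasons, listed by arm.

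The cost is two items on an existing question and one small table, with no extra visits or staff. Recruitment is expected to run to March 31, 2026. For any guesses already recorded, the table by arm and FAC status can still be made, but the new items will be missing. The intervals will be wide (about ±0.49 per arm, wider by FAC status), so modest leakage such as 20% cannot be confirmed or excluded. The table should be read descriptively, alongside the stated reasons.

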### Randomization

Participants will be stratified by stroke type and randomly allocated to either the RAGT or CGT group using a computer-generated permuted block randomization method with permuted block sizes of two and four. Random allocation will be performed by an independent researcher not involved in the assessments, using the Research Electronic Data Capture tool [24].

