In addition, to understand participant characteristics, the following data will be collected at baseline: age; sex; height; weight; disease type; affected side; days post-stroke onset at admission, assessment, and discharge; National Institutes of Health Stroke Scale (NIHSS) score; GCS score; SIAS motor function scores for the lower extremities; trunk function; sensory function in the lower extremities; tone in the lower extremities; function in the lower extremities on the unaffected side; and visuospatial function. The NIHSS is a reliable and validated index for assessing stroke severity [39–41]; it evaluates consciousness, gaze, visual field, facial paralysis, paralysis of the extremities, ataxia, sensory disturbance, aphasia, dysarthria, elimination issues, and neglect, with scores ranging 0–42. A score of 0 is considered normal, while 42 indicates the most severe condition. The GCS consists of three items, namely eye opening, verbal response, and motor response. Eye opening is scored from 1 to 4, verbal response from 1 to 5, and motor response from 1 to 6. The total GCS score is defined as the sum of the scores of these three items, ranging 3–15, with 3 indicating severe impairment and 15 indicating normal responsiveness.

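### Randomisation is stratified by stroke type, but the log-rank test, generalized Wilcoxon test and hazard ratio are described without that stratum

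*Protocol article*

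**What the plan says.** Under Randomization, the protocol article states: "Participants will be stratified by stroke type and randomly allocated to either the RAGT or CGT group". The method is a "permuted block randomization method with permuted block sizes of two and four". The eligibility criteria admit infarction and haemorrhage, so there are presumably two strata.

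Under Analytical methods, the comparison of time to gait independence is specified thus: "the log-rank test will evaluate the significance of differences in the" Kaplan–Meier curves of the two groups. A generalized Wilcoxon test supplements it, and a hazard ratio is to be estimated as the effect size. No stratum or covariate is attached to any of the three, and no model is named for the hazard ratio.

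Under Clinical outcomes, baseline severity is recorded, including "SIAS motor function scores for the lower extremities; trunk function", with the stated purpose of describing the participants.

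On size, the article says "We aim to enroll 32 participants" and that "the sample size was not calculated based on statistical testing power". The Discussion calls the clinical findings exploratory. It adds that the pilot's effect sizes will not be used directly to size a definitive trial.

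**The concern.** Stratified allocation balances the arms on stroke type. If stroke type is prognostic, that balance removes some of the chance variation between arms. A test that ignores the stratum still counts this variation as noise, so it rejects less often than its nominal level under the null and has less power under an effect.

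The hazard ratio has a related property: it is non-collapsible. Leaving out a prognostic factor gives a marginal hazard ratio that lies nearer to 1 than the hazard ratio within strata, even when the arms are perfectly balanced.

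At stake is a modest amount of power, and which hazard ratio the pilot reports. The article says this effect size is estimated partly to supply data for future trial design, and it calls the outcome the leading candidate for a future endpoint. The analysis is therefore likely to serve as a template.

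**Working it through.** **The plan's own figure.** The only sample-size figure is the retention interval: "a retention of 90% can be estimated to within a 95% confidence interval (CI) ranging from 75–96" per cent. The Wilson score interval with p = 0.90, n = 32, z = 1.96 has

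- centre (0.90 + 3.8416/64) / (1 + 3.8416/32) = 0.9600/1.1201 = 0.857
- half-width 1.96 × √(0.09/32 + 3.8416/4096) / 1.1201 = 0.107

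This gives 75.0–96.4%, which reproduces the stated interval. The article gives no power, significance level, effect size or event count.

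**Background power.** The article's Background puts recovery of gait at 41–85%. Applied to 32 participants, this is 0.41 × 32 ≈ 13 to 0.85 × 32 ≈ 27 events. With equal arms, an assumed two-sided 5% level and an assumed hazard ratio (HR) of 2, Schoenfeld power is Φ(√d/2 × ln 2 − 1.96):

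- d = 13: Φ(1.25 − 1.96) = 24%
- d = 27: Φ(1.80 − 1.96) = 44%

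Power is low whichever analysis is chosen.

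**Simulated cost of omitting the stratum.** From the documents: 32 participants, allocation stratified by stroke type, 8-week limit. Assumed: two strata, true HR of 2 within strata, and the prognostic strengths shown.

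- Setting A: permuted blocks of 2 and 4 within strata, 40/60 stratum split, 50% control achievement, continuous times, Cox likelihood-ratio test, 3,000 runs per row, about 20 events.
- Setting B: 16 per stratum, 55% control achievement, weekly visits, log-rank test. It was run twice; the first run used 1,500 trials per row.

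Power in %, unstratified v stratified:

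| Stroke-type HR | A | B, run 1 | B, run 2 |
|---|---|---|---|
| 1 | 33.1 v 32.4 | 36 v 36 | 37 v 36 |
| 1.5 | 33.2 v 33.5 | – | – |
| 2 | 29.4 v 31.8 | 31.5 v 33.5 | 32 v 35 |
| 3 | 25.2 v 32.7 | – | 26 v 34 |
| 4 | – | 19.5 v 32.9 | 21 v 33 |

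Stratifying gains 0.3 points at HR 1.5, 2–3 at HR 2, 7.5–8 at HR 3 and 12–13 at HR 4. It loses 0–1 point at HR 1. The simulation error of one power figure is about √(0.33 × 0.67/3000) = 0.9 points in A and √(0.33 × 0.67/1500) = 1.2 points in run 1 of B, so the gaps at HR 1.5–2 are close to noise. With no treatment effect and stroke-type HR 4, the unstratified test in B rejects about 3% of the time (2.5% in run 1) instead of 5%.

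**Hazard ratio and its standard error (setting A).**

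| Stroke-type HR | Median HR, unadjusted v stratified | SE of log HR, unadjusted v stratified |
|---|---|---|
| 1 | 2.02 v 2.03 | 0.465 v 0.471 |
| 1.5 | 1.98 v 2.01 | 0.466 v 0.474 |
| 2 | 1.94 v 2.03 | 0.462 v 0.477 |
| 3 | 1.87 v 2.05 | 0.461 v 0.480 |

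Stratifying raises the standard error slightly. Around an estimate of 2, a standard error of 0.46 gives exp(0.693 ± 0.902) = 0.81 to 4.93, and 0.48 gives exp(0.693 ± 0.941) = 0.78 to 5.12.

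**A severity covariate.** With stroke-type HR 1.5 and a severity HR of 2 per SD, setting A gives median HRs of 1.78 unadjusted, 1.78 stratified and 2.03 stratified plus covariate, with power 24%, 25% and 32%. At a severity HR of 1.5 per SD, power is 30%, 30% and 33%. In a companion run that tested the covariate model by a Wald test, power at severity HR 2 was 23%, no better than the 25% without adjustment. Any gain therefore depends on the test as well as on the assumed strength.

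**The case against.** The strongest reply is that the article is silent rather than wrong. It condenses a fuller protocol, names no model for the hazard ratio and excludes no stratum; model form is commonly left to an analysis plan. That stands for the hazard ratio. It stands less well for the tests: the section lists its methods in detail and presents each test as a plain two-group comparison, although a stratified design precedes it. If the full protocol already stratifies the analysis, a clarifying phrase in the article is enough.

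It is also fair to say that the large losses need an assumed stroke-type HR of 3–4, for which the documents offer no support, and that power is poor either way.

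A reader might infer more than the documents support:

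- *That the unstratified analysis wastes precision.* For the hazard ratio the reverse holds: its standard error is slightly smaller without the stratum. What can be lost is power.
- *That the unadjusted hazard ratio is biased.* It validly estimates a marginal quantity, which differs from the within-stratum one when stroke type is prognostic and treatment has an effect.
- *That omitting baseline severity lets chance imbalance dominate the result.* The documents give no prognostic strength for severity, and eligibility already restricts the lower-limb motor total to 6 or less and the ambulation category to 1 or less. With roughly 13–27 events, adjusting for every severity measure is not workable.
- *That the pilot hazard ratio will fix the size of the next trial.* The Discussion says it will not be used directly for that.

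**Conclusion.** The mismatch is real but minor. Allocation uses stroke type, and the described tests and hazard ratio do not. The unstratified test does not inflate the false-positive rate; it is conservative if stroke type is prognostic, and the unadjusted hazard ratio then sits nearer to 1 than the within-stratum value.

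With a true HR of 2 and about 20 events, the power loss is about 0–3 points for a stroke-type HR of 1.5–2 and about 7–13 points for 3–4, against about 1 point lost by stratifying when stroke type is irrelevant. These figures rest on assumed prognostic strength, event rate, stratum split and significance level. Because the trial is not powered for efficacy and its clinical results are exploratory, no stated decision turns on the difference. The case for change is that it costs almost nothing and makes the analysis match the design.

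**What to change.** In Analytical methods, state that the log-rank and generalized Wilcoxon tests are stratified by stroke type, and that the hazard ratio with its 95% confidence interval comes from a Cox model stratified by stroke type. Report the unadjusted hazard ratio and the Kaplan–Meier curves alongside.

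Optionally, name one baseline severity covariate in advance for a supportive analysis, for example the SIAS lower-limb motor total, which runs from 0 to 6 at entry.

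The cost is one or two sentences and no new data. The statistical price is a slightly wider interval for the hazard ratio (standard error of its log about 0.47–0.48 rather than 0.46) and about 1 point of power if stroke type turns out not to be prognostic.

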### Interventions

The study schedule is illustrated in Fig. 2. Participants will undergo the intervention during their hospitalization at Fujita Health University Hospital. The intervention will continue until participants achieve an FAC score of ≥ 3 or for up to 8 weeks from the start of training. Participants in both the RAGT and CGT groups will receive rehabilitation for 180 min per day, 7 days per week. Both groups will undergo gait training for 60 min per day [30] and non-gait training for 120 min per day. The RAGT group will undergo RAGT for 40 min per day and CGT for 20 min per day, for 6 days a week, with an additional 60 min of CGT once per week. The CGT group will undergo CGT for 60 min, 7 days per week (Fig. 2).

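### One censoring rule covers every non-achiever, so 1 − KM will not estimate the percentage reaching gait independence if participants die or leave before week 8

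*Protocol article*

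**What the plan says.** The Analytical methods section of the protocol article fixes the estimator, the test and the censoring rule:

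- Estimator: "The cumulative incidence of gait independence will be analyzed using the Kaplan–Meier method".
- Test: "the log-rank test will evaluate the significance of differences in the Kaplan–Meier curves between groups". A generalized Wilcoxon test is added as a supplement, and a hazard ratio is to be estimated.
- Other summaries: incidence at the end of the intervention, the median time, and "the restricted mean survival time until the end of the intervention will be calculated".
- Censoring: "Individuals who do not achieve gait independence during the intervention period will be censored".

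Reasons for dropout are to be recorded, but no analysis uses them.

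Three other places bear on who could be censored early. The Interventions section sets the place, "Participants will undergo the intervention during their hospitalization at Fujita Health University Hospital", and the duration: until FAC ≥ 3 or "for up to 8 weeks from the start of training". The Clinical outcomes section promises fixed visits: "However, assessments at 4 and 8 weeks and discharge will always be performed". The Discussion lists the absence of long-term follow-up as a limitation and leaves assessments after discharge to future trials.

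The Clinical outcomes section also defines the primary outcome as both the days to gait independence and the percentage of individuals who achieve it.

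**The concern.** Kaplan–Meier treats a censored person as someone who would have gone on to reach FAC ≥ 3 at the same rate as those still under observation. That is safe for a participant who reaches week 8 without walking, because observation stops there for everyone. It is not safe for the other ways of leaving, and the rule does not separate them.

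A participant who dies before walking can no longer have the event. Censoring that person makes 1 − KM describe a hypothetical setting in which the dead continue to recover, so it no longer estimates the percentage named as primary outcome. A participant discharged or transferred before week 8 may have left because recovery was going well or badly, and then the censoring carries information about the outcome.

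The participants start treatment within 7 days of a stroke, with severe leg paresis and FAC ≤ 1, so such exits are foreseeable. Preliminary efficacy estimates are the second stated objective. The protocol also calls this outcome the leading candidate endpoint for later trials, so its definition is likely to carry forward.

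**Working it through.** **The plan's own figure.** The document gives no figure for the time-to-event analysis. Its one statistical figure is the 95% CI of 75–96% for 90% retention with n = 32. The Wilson interval reproduces it:

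- centre = (0.90 + 3.8415/64) / (1 + 3.8415/32) = 0.857
- half-width = 1.96 × √(0.09/32 + 3.8415/4096) / 1.120 = 0.107
- limits 75.0% and 96.4%

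The present point does not affect that figure.

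**Inputs for the check.** From the document: an 8-week maximum, 1 − KM as estimator, all non-achievers censored, 32 participants, and a background range of 41–85% for recovery of gait. Assumed, because the document gives no rates: constant cause-specific hazards, 1 − KM of 60% at week 8, and a net 8-week probability *c* of a competing event (one that would apply in the absence of walking) between 0 and 40%.

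**Formulas.** With F = 1 − KM at week 8, the cumulative hazards over 8 weeks are A = −ln(1 − F) for walking and B = −ln(1 − c) for the competing event.

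- True cumulative incidence of walking = A/(A + B) × [1 − (1 − F)(1 − c)]
- Observed share with the competing event = B/(A + B) × [1 − (1 − F)(1 − c)]

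Example with F = 0.60 and c = 0.30: A = 0.9163, B = 0.3567, A/(A + B) = 0.7198, and 1 − 0.4 × 0.7 = 0.72. The incidence is 0.7198 × 0.72 = 51.8%, and the observed competing share is 72.0 − 51.8 = 20.2%.

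| c | 1 − KM | True incidence | Overstatement (points) | Observed competing events |
|---|---|---|---|---|
| 0% | 60% | 60.0% | 0 | 0% |
| 5% | 60% | 58.7% | 1.3 | 3.3% |
| 10% | 60% | 57.4% | 2.6 | 6.6% |
| 15% | 60% | 56.1% | 3.9 | 9.9% |
| 20% | 60% | 54.7% | 5.3 | 13.3% |
| 30% | 60% | 51.8% | 8.2 | 20.2% |
| 40% | 60% | 48.8% | 11.2 | 27.2% |

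So about 10% observed (0.099 × 32 ≈ 3 participants) gives about 4 points, and about 20% (0.202 × 32 ≈ 6.5) gives about 8 points. Over c = 5–40%, the overstatement is 0.9–8.2 points at 1 − KM = 41% and 1.5–13.3 points at 85%.

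**Contrast between arms.** Let the walking hazard be equal in both arms (1 − KM = 60%) and let c be 10% in one and 30% in the other. Kaplan–Meier shows no difference, while the true incidences differ by 57.4 − 51.8 = 5.6 points. With 5% and 20% the gap is 58.7 − 54.7 = 4.0 points. The log-rank test is not wrong here: the cause-specific hazards are equal. It answers a different question from the percentage achieving independence.

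**Exits related to prognosis.** Assume half the participants are fast recoverers (90% walking by week 8 if never transferred) and half slow (30%). The true value is 0.5 × 0.90 + 0.5 × 0.30 = 60%. Simulation with 400,000 participants gives:

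- slow recoverers leave early (net probability 50%, against 10% for fast): KM 63.9%
- fast recoverers leave early (50%, against 10% for slow): KM 56.3%
- leaving unrelated to prognosis (30% each): KM 60.0%

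The direction depends on who leaves.

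**The passages side by side.** Interventions ties treatment to the hospital stay. Clinical outcomes promises a week-8 assessment in all cases. The Discussion defers assessments after discharge. A participant discharged at, say, week 5 therefore has a week-8 FAC under one section and apparently none under another. If it is obtained, the censoring rule can discard it.

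**The case against.** A reader might infer that treatment ends at discharge, often before week 8, and that the primary estimate is therefore biased upwards. The document does not support that. The ends it states are FAC ≥ 3 or 8 weeks. That earlier discharge also ends treatment is a strong inference from the in-hospital setting, but it is not written. No length of stay, transfer rate or mortality is given. If every non-achiever stays to week 8, all censoring is administrative and there is no bias. For transfers the bias can go either way.

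A reader might also infer that the arms are distorted because faster walkers go home sooner. Mostly those people have already reached FAC ≥ 3, so their discharge censors nothing. Only exits of non-achievers matter. Nor does censoring deaths spoil every quantity: the log-rank test and hazard ratio remain valid for the cause-specific hazard. Eight weeks is also the natural limit for the restricted mean.

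There are mitigating features too. The crude percentage achieving independence is itself named as primary and, taken over all randomized participants, would count deaths and early exits as non-achievers. Reasons for dropout are recorded. With 16 per arm the standard error of a 60% incidence is √(0.6 × 0.4/16) ≈ 12 points, larger than the illustrated bias.

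These arguments limit the size and certainty of the problem. They do not remove it: the rule is written down rather than left open, it makes no distinction by reason, and 1 − KM will not match the named percentage once a participant dies before walking.

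**Conclusion.** The point holds conditionally. As written, the rule is correct for participants who complete 8 weeks. For deaths before FAC ≥ 3 it makes 1 − KM too high as an estimate of the percentage achieving independence. For discharge, transfer or withdrawal related to prognosis it biases the curve, and the quantities derived from it, in a direction that cannot be known beforehand. In that second case the log-rank test and hazard ratio are affected as well.

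The illustrated size is about 4 to 8 points at 1 − KM = 60% with about 10–20% observed competing events, and zero with none. It rests on constant hazards and on exit rates that the document does not supply.

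Severity is moderate. Clinical findings are called exploratory, effect sizes will not directly size the next trial, and no progression criterion uses the Kaplan–Meier estimate.

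**What to change.** In Analytical methods, replace the single censoring sentence with rules by reason:

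1. Set one horizon of 56 days for the cumulative incidence and the restricted mean. Name its origin, since days to independence are counted from baseline but the 8 weeks from the start of training.
2. Treat death before FAC ≥ 3 as a competing event and report the Aalen–Johansen cumulative incidence. Keep the log-rank test and hazard ratio, labelled as cause-specific comparisons. Gray's test is optional.
3. Censor only at 8 weeks or at true loss to follow-up.
4. Add a sensitivity analysis that counts early-discharged or withdrawn non-achievers as not achieving by week 8.
5. Reconcile Interventions, Clinical outcomes and the Discussion on whether the week-8 FAC is obtained after early discharge, and use it where it is.

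The cost is revised wording and a few lines of code, using dropout reasons already collected. The reported incidence may be slightly lower. A FAC obtained after discharge covers time off treatment, and the date of an event first seen there is known only to lie between the last in-hospital assessment and week 8. Whether that assessment is available is not settled by the document, so item 4 is needed in any case.
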